### Confirmatory factor analysis

By performing confirmatory factor analysis, the hypothesized model will be compared with the observed model in the real world. Confirmatory factor analysis will be performed in LISREL software [45].

### Reliability

The reliability of PWSSQ will be assessed using internal consistency and stability measures. Internal consistency will be evaluated by calculating the Cronbach’s alpha coefficient for PWSSQ and its subcategories. An alpha value of 0.70 or higher was deemed acceptable. The test–retest reliability of PWSSQ and its subcategories over a two-week period will be determined using the intraclass correlation coefficient (ICC), with ICCs between 0.7 and 0.8 indicating adequate stability. Items that demonstrate poor reliability will be excluded from factor analysis to ensure construct validity. The instrument will be designed based on the psychometric properties outlined in the Consensus-based Standards for the Selection of Health Status Measurement Instruments (COSMIN) checklist.

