Although sexual performance generally decreases with increasing age, in the study of Addis et al. (2006), the sexual activities and behaviors of 2109 women aged 40 to 69 years were examined, and it was found that approximately 75% of them were sexually active [3]. In many societies, cultural concepts and experiences affect a woman's perception of menopause and her sexual performance during this period. For some women, menopause causes a decrease in sexual activity, and even sexual performance becomes less enjoyable during this time. However, for others, sexual activity during menopause is associated with a sense of freedom due to the lack of fear of pregnancy during this period [4]. One important aspect that is often ignored or considered taboo in the middle-aged and elderly population is sexual satisfaction [5, 6]. Sexual satisfaction is a component related to human sexuality and is known as the last stage of the sexual response cycle. Sexual satisfaction is defined as an emotional response resulting from the mental evaluation of positive and negative things in a sexual relationship [7]. The concept of sexual satisfaction can be divided into two types: satisfaction from sexual activities and emotional-emotional satisfaction [8]. However, other researchers define sexual satisfaction based on individual expectations, that is, the degree of sexual activity that meets the individual's expectations [9]. In fact, sexual satisfaction is considered not only one of the dimensions of sexual health but also a sexual right and the result of sexual well-being and overall health [10, 11]. Satisfaction with sexual relationships is one of the important factors of satisfaction with one’s married life. People who are sexually satisfied report significantly better quality of life than those who are not sexually satisfied [12]. One of the factors influencing sexual satisfaction is estrogen, which plays an essential role in sexual desire. Estrogen plays a role in improving the elasticity of pelvic tissues for sexual intercourse. When estrogen is not produced in a sufficient amount before menopause, vaginal dryness may occur. A low level of estrogen is one of the predictors of sexual dysfunction during menopause [13, 14]. Menopause may directly or indirectly affect women's sexual satisfaction. Vasomotor symptoms associated with menopause, physical symptoms, body image changes, and depression and anxiety resulting from menopause are associated with decreased sexual performance and decreased sexual satisfaction and pleasure [15]. A 2013 review study in France revealed that variables and factors such as a) demographic factors as well as physical and mental health status, b) variables related to intimate relationships and sexual response, c) variables related to social support and family relationships, and d) cultural beliefs and values such as religion all play a role in explaining sexual satisfaction. According to the findings of this study, there is a lack of theoretical models to explain sexual satisfaction and the combination of influencing factors on sexual satisfaction [7]. Sexual satisfaction is important for sexual researchers for two reasons. First, sexual satisfaction provides a mechanism through which to examine relationship partner performance. Second, sexual satisfaction is a predictive structure of other aspects of the relationship, such as marital quality and stability [16]. The concept of sexual satisfaction in menopausal women is very different from that in premenopausal women, and this difference is due to aging and physical, hormonal, cultural, and psychological changes. To determine the methods of achieving sexual satisfaction within the capabilities of a menopausal woman, we need to investigate sexual satisfaction in this special group. The importance of examining the concept of sexual satisfaction from the point of view of menopausal women is necessary for sexual education and sexual therapy because the type of education and the content of education change due to changes in menopause are very different from those in pre-menopause [5, 17, 18]. Menopausal women, as a special group, have special assignments that distinguish them from other age groups to some extent and that affect their health. Therefore, the first step in the development and construction of a measurement tool is to describe the nature of the concept. The more clearly the concept is defined, the easier it is to write its measurement questions [4, 19]. On the other hand, the existing tools in the field of women's sexual satisfaction are not specifically designed for this age group (menopausal women) and do not have the necessary comprehensiveness and adequacy to investigate sexual satisfaction in menopausal women [20, 21]. Therefore, the current study aims to define the concept of sexual satisfaction based on the experiences and views of postmenopausal women, and the studies conducted, based on the hybrid explanatory model, and then, based on the presented concept, to design and psychometrically assess the sexual satisfaction of postmenopausal women. Improving sexual satisfaction in this large and growing population.

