### Phase 2: the quantitative part of the study

This part is a study of instrument design and validation. To design a tool for measuring the sexual satisfaction of postmenopausal women, sexual satisfaction items will be obtained from the first stage of the research with a hybrid model, and then its validity and reliability will be assessed. The above steps are based on Waltz's model, which includes two sub-studies of instrument design and psychometrics [37].

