### Construct validity

In this research, exploratory and confirmatory factor analysis will be used [37, 42].

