### Exploratory factor analysis (EFA)

The goals of exploratory factor analysis are instrument development, theory development, and data reduction [43]. The number of samples required for factor analysis varies from 3–10 samples per item. The number of samples required for factor analysis varies from 3–10 samples per item [38]. Menopausal women between the ages of 40 and 70 who did not have a known mental illness or limiting physical illness, who did not use sex hormones, who could speak Farsi fluently, who were willing to share their experiences regarding the research topic, and who had engaged in sexual activity with their spouses were included in this study. Bartlett’s test of sphericity will be used to determine the operability of the data, and the Kaiser‒Meyer‒Olkin (KMO) index will be used to determine the adequacy of the data. The KMO index ranges from 0 to 1. A KMO greater than 0.7 is interpreted as an acceptable and large sample size that is suitable for EFA. Based on the initial results of the factor analysis, orthogonal and oblique rotation methods were used to better present the data [44]. Factors were named according to the common meaning of the items.

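### The 0.70 alpha rule for the whole PWSSQ carries no dimensionality condition, so a questionnaire made of unrelated subscales can meet it

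*Protocol article*

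**What the plan says.** The Reliability section fixes both the scope and the criterion for internal consistency. The scope is "Internal consistency will be evaluated by calculating the Cronbach’s alpha coefficient for PWSSQ and its subcategories". The criterion is "An alpha value of 0.70 or higher was deemed acceptable". No separate criterion is given for the whole scale, and nothing must be shown about its structure before its alpha is read.

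Several dimensions are expected. The Background reports that "The concept of sexual satisfaction can be divided into two types". The exploratory factor analysis section speaks of factors in the plural ("Factors were named according to the common meaning of the items"), and the Reliability section speaks of subcategories.

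Structure is handled under construct validity: "In this research, exploratory and confirmatory factor analysis will be used". On rotation, "orthogonal and oblique rotation methods were used to better present the data". The two parts of the plan are joined by one sentence only, and it runs from reliability to factor analysis: "Items that demonstrate poor reliability will be excluded from factor analysis to ensure construct validity".

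The number of items is not stated. It depends on Phase 1, since "sexual satisfaction items will be obtained from the first stage of the research with a hybrid model".

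**The concern.** Alpha depends on the average correlation over all item pairs and on the number of items. It does not show how the correlation is arranged. One common construct, or several separate blocks that have nothing to do with each other, can give the same value. For a scale expected to have several factors, a whole-scale alpha above a cut-off therefore does not show that the items belong together.

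The study exists to produce and validate this instrument. As written, it could report factors that are uncorrelated and, in the same paper, call the whole PWSSQ acceptably consistent. If a user then added the items into one score, two women with equal scores could have quite different profiles, and the score would have no single meaning.

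**Working it through.** **Stated figure.** The only number on this point is the 0.70 threshold. It is a criterion, so there is nothing to reproduce. The question is what kinds of scale can meet it.

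**Inputs.** From the article: threshold 0.70, applied to the whole PWSSQ and its subcategories; several factors expected; orthogonal rotation allowed. Assumed, because the article gives none of them: *m* subscales of equal size, *p* items each, *k = m × p* items in all, a common correlation *r* between items of the same subscale, and zero correlation between subscales.

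**Formulas (standardized alpha).**
- Mean inter-item correlation: r̄ = r(p − 1)/(k − 1)
- Whole scale: α = k·r̄ / [1 + (k − 1)·r̄]
- One subscale: α = p·r / [1 + (p − 1)·r]

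**Worked cases.**
- 3 × 10 items, r = 0.25 (loadings of 0.5): r̄ = 0.25 × 9/29 = 0.0776; whole-scale α = 2.328/3.25 = 0.716; subscale α = 2.5/3.25 = 0.769.
- 3 × 10 items, r = 0.3: r̄ = 0.3 × 9/29 = 0.0931; whole-scale α = 2.793/3.7 = 0.755; subscale α = 3/3.7 = 0.811.
- 3 × 5 items, r = 0.4: r̄ = 0.4 × 4/14 = 0.1143; whole-scale α = 1.714/2.6 = 0.659; subscale α = 2/2.6 = 0.769.

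| Subscales × items | r within | Subscale α | Whole-scale α | Whole scale meets 0.70 |
|---|---|---|---|---|
| 3 × 5 | 0.4 | 0.769 | 0.659 | no |
| 3 × 5 | 0.5 | 0.833 | 0.714 | yes |
| 3 × 8 | 0.3 | 0.774 | 0.707 | yes |
| 3 × 10 | 0.2 | 0.714 | 0.665 | no |
| 3 × 10 | 0.25 | 0.769 | 0.716 | yes |
| 3 × 10 | 0.3 | 0.811 | 0.755 | yes |
| 3 × 10 | 0.5 | 0.909 | 0.846 | yes |
| 4 × 10 | 0.4 | 0.870 | 0.803 | yes |
| 5 × 5 | 0.5 | 0.833 | 0.694 | no |

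**Would the subscale alphas give a warning?** No. With uncorrelated subscales of equal size, whole-scale α divided by subscale α equals [k/(k − 1)] / [p/(p − 1)], which is below 1 whenever there is more than one subscale. For 3 × 10 it is (30/29)/(10/9) = 0.931, and 0.811 × 0.931 = 0.755. So whenever the whole scale passes under this structure, every subscale passes too.

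**What does length contribute?** It lowers the mean correlation needed: r̄ = 0.7/[k − 0.7(k − 1)], which is 0.7/6.7 = 0.104 for 20 items, 0.7/9.7 = 0.072 for 30 and 0.7/12.7 = 0.055 for 40. But if all inter-item correlations are zero, alpha is 0 at any length. Adding unrelated 10-item blocks with r = 0.3 slightly lowers alpha: 0.811 for one block, 0.768 for two, 0.755 for three, 0.748 for four, 0.745 for five. The pass comes from the number of items per subscale and their correlation within it.

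**The case against.** The strongest reply is that the plan does not ask alpha to settle dimensionality. Alpha sits under reliability, structure is left to exploratory and confirmatory factor analysis, and subscale alphas are already planned. An oblique solution, or a confirmatory model with correlated factors, would show unrelated dimensions. Zero correlation between subscales is also an extreme case for items written from one working definition, and the number of items and factors cannot be known before Phase 1. Much of this stands. It limits the point to the acceptance rule for the whole scale, and it means that the size can be shown only as a range. It does not remove the point, because no sentence makes the whole-scale verdict depend on the factor results, an orthogonal rotation cannot show factor correlations, and the only stated link places some reliability screening before the factor analysis.

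Three stronger readings are tempting, and the article does not support them.
- *That a long questionnaire passes by length alone.* The arithmetic above rules this out.
- *That the protocol takes alpha as proof of one dimension, or will endorse a total score because alpha reaches 0.70.* It says neither. It defines no total score and states no decision rule for one.
- *That planners will act on the total.* The Discussion expects planners and health service providers to benefit from the tool, but mentions no total. Use of a total is an inference from the fact that alpha is calculated for the whole PWSSQ.

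**Conclusion.** The point holds in a limited form. The stated rule can call the whole PWSSQ internally consistent when its subscales are unrelated, and neither the subscale alphas nor any stated link to the factor analyses would stop this. Under the assumed structure (equal, mutually uncorrelated subscales), whole-scale alpha runs from 0.659 to 0.846 in the table, on both sides of 0.70. So the rule does not always pass such a scale, but it cannot be relied on to detect one. The cases illustrate what is possible and give no probability. That the PWSSQ will have several dimensions is implied by the article but not yet established. This is a weakness in a stated acceptance rule that is cheap to correct, and it does not undermine the planned factor analyses.

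**What to change.** In the Reliability section, apply the 0.70 acceptance rule to the subscales defined by the factor analysis. State that a whole-scale alpha, or any total score, will be interpreted only if the same data support a common construct, shown by the factor correlations from an oblique exploratory solution or the confirmatory model, or by a second-order factor. Otherwise report subscale results only.

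The cost is a few lines of wording and a little more analysis of data that will be collected anyway, with no extra participants. The possible loss is that no reliability claim for the whole questionnaire can be made.

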## Discussion

Menopause refers to the permanent cessation of menstruation. Women in developed countries live approximately 30 years, or more than one-third, of their lives during the postmenopausal period [46]. Sexual intercourse is an essential component of women's health care at all ages because sexual dissatisfaction and general well-being are closely related. Estrogen and androgen deprivation may manifest with multisystem consequences, including effects on tissues devoted to sexual function [47]. Vaginal dryness, bleeding during intercourse, and dyspareunia are all common complaints of menopausal women, and these symptoms on average lead to decreased libido and decreased sexual satisfaction in menopausal women [48, 49]. Understanding the concept of different aspects of sexual concepts is necessary for the correct assessment of women's health, but due to the multiple nature of sexual reality, scientific truths cannot be obtained without discovering its dimensions in a natural context [11, 50, 51]. Therefore, the concept of sexual satisfaction in postmenopausal women is very different from that in premenopausal women [17].

To discover the methods of achieving sexual satisfaction within the capabilities of a menopausal woman, we need to investigate sexual satisfaction in this special group because the type of training and the content of training are very different due to the changes in menopause compared to pre-menopause. In fact, evaluating the interaction between various predisposing, accelerating, and maintaining sexual satisfaction factors requires extensive analysis. When a single questionnaire is used for these different age groups, the questions asked may not accurately measure the concept of sexual satisfaction in postmenopausal women because the definition of the concept of sexual satisfaction in postmenopausal women is different from that in premenopausal women.

In recent decades, research on women's sexual satisfaction has attracted much attention, and various tools have been used to measure it. One of the most widely used tools in the world and Iran is the sexual satisfaction tool of Larson et al. (1998) [52]. This tool is not specific for women during menopause, and this tool is old. In addition to the fact that some items overlap with sexual performance and do not distinguish between sexual satisfaction and distress, it is suitable for assessing romantic relationships. Additionally, other tools were not designed for menopausal women and are outdated, sexual expression changes over time, and information needs are necessary according to these changes [53]. It is expected that by designing this tool and evaluating the sexual satisfaction of postmenopausal women, it will be possible to help the planners and providers of health services and specialists of different scientific groups with proper planning, appropriate allocation of resources and facilities based on the reported priorities to improve the sexual satisfaction of postmenopausal women and, ultimately, help improve the sexual health of women during menopause, the number of whom is increasing daily. The strength of this study is the use of the hybrid conceptual method in the first stage of the study, which will provide comprehensive information for the design of the desired tool items. This protocol has certain limitations similar to those of other qualitative approaches, such as sampling only in Iran and limited generalizability, which can be reduced with maximum diversity in sampling. They should not talk about their private sexual issues, which should be done by assuring them of confidentiality to reduce this challenge.

## Data Availability

No datasets were generated or analyzed during the current study.

## Abbreviations

PWSSQ: Postmenopausal Women's Sexual Satisfaction Questionnaire
WHO: World Health Organization
CVR: Content Validity Ratio
CVI: Content Validity Index
EFA: Exploratory Factor Analysis
KMO: Kaiser–Meyer–Olkin
ICC: Intraclass Correlation Coefficient
COSMIN: Consensus-based Standards for the Selection of Health Measurement Instruments
